### Study design {8}

This will be a 2-center, factorial design, equal proportional distribution, superiority trial conducted in outpatient endocrinology clinics at two tertiary hospitals in Chengdu, China, which will be conducted from 2021 to 2023. 

In reporting the protocol for this study, we followed the SPIRIT 2013 checklist. Individuals will be randomly allocated to the Control group, Reminder group, App group, and App + Reminder group. Flow diagram of the study is shown in Fig. 1.

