## Assignment of interventions: allocation

### Sequence generation {16a}

Before enrollment began, two sets of random numbers were generated using EXCEL by people not involved in the study. The serial number of each set was determined in advance and placed in an opaque, sequentially numbered envelope. Upon completion of the baseline assessment, eligible participants will be randomly (proportionally) assigned to one of four groups.

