## Statistical methods

### Statistical methods for primary and secondary outcomes {20a}

Data will be analyzed applying SPSS 23.0 (IBM, Chicago, IL, USA). Data will be expressed as mean ± standard deviation or as *n* (%) in the case of categorical data, and differences between the four groups will be assessed for significance using the chi-squared test in the case, analysis of variance in the case, or non-parametric rank-sum test in the case of skewed continuous data. Differences between different time points within each group will be assessed for significance using generalized estimation equation. These models will include intervention variables, time as a categorical variable represented by dummy variables, the interaction between intervention and time, and baseline values. Differences associated with *P* < 0.05 will be considered significant.

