### Methods for additional analyses (e.g., subgroup analyses) {20b}

We may analyze by comparing two study sites or educational levels.

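### The listed model terms leave out study centre in a two-centre trial; adding it costs one degree of freedom and recovers a little precision

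*Protocol article*

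**What the plan says.** Study design {8} describes a "2-center, factorial design, equal proportional distribution, superiority trial". Section {20a} assigns comparisons of the four arms to simple tests: "differences between the four groups will be assessed for significance using the chi-squared test in the case, analysis of variance in the case", with a rank-sum test for skewed data. No covariate or centre factor is attached to these. It then introduces a second method: "Differences between different time points within each group will be assessed for significance using generalized estimation equation". The terms of that model are spelled out: "These models will include intervention variables, time as a categorical variable represented by dummy variables, the interaction between intervention and time, and baseline values".

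Site returns only under additional analyses {20b}, as an option: "We may analyze by comparing two study sites or educational levels".

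On allocation, {16a} says that "two sets of random numbers were generated using EXCEL". Neither {16a} nor {16b} says whether there was one set per hospital, and stratification is not mentioned.

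Two further facts bear on the point. Under Outcomes {12}, all HbA1c samples go to a single external laboratory. In Table 1 and {18a}, monitoring frequency is collected only at months 3 and 6, so it has no baseline value.

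**The concern.** Outcome levels can differ between two hospitals through case mix, local care or local assessors. If centre is not in the model, the part of that difference that no other term explains counts as residual noise.

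The consequence depends on how allocation was done. If it was done separately by hospital, the arms are balanced on centre by design, but the analysis does not take credit for that, so its standard errors are slightly too large. If it was not, a chance imbalance between hospitals stays in the estimate where a known two-level variable could have removed it. In both cases precision is lost that could be had at almost no cost.

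The loss is most complete where the listed terms give no protection: the unadjusted four-group analysis of variance, and monitoring frequency, which is a secondary outcome linked to the second study aim.

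**Working it through.** **Inputs.** From the documents: two centres ({8}); N = 220 before the dropout allowance, effect size 0.2 with an F-test, two-sided alpha 0.05 ({14}). Read as Cohen's f, 0.2 is a difference of 2 × 0.2 = 0.4 SD between two equal halves of the trial, 110 against 110. The documents give no centre effect and no centre sizes. Assumed here: equal-sized centres, and a residual centre difference D of 0.2 to 0.5 SD.

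**The plan's own figure.** There is none for a centre effect. The 220 serves only as the reference size. A one-degree-of-freedom F-test with f = 0.2 has power 0.840 at N = 220, and the normal approximation used below gives 0.843. That this is not the stated 0.9 is a separate matter on which nothing here relies.

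**Case A: allocation separate by hospital.** Centre then cancels from the treatment contrast, so the true standard error is √(2/110) = 0.135 SD. A model without centre reports one larger by √(1 + D²/4).

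- Type I error = 2 × [1 − Φ(1.96 × √(1 + D²/4))]
- Power = Φ(0.4/0.1348 − 1.96 × √(1 + D²/4)), with 0.4/0.1348 = 2.966

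| D (residual SD) | D²/4 | Type I error | Power without centre |
|---|---|---|---|
| 0.2 | 0.0100 | 0.0489 | 0.841 |
| 0.3 | 0.0225 | 0.0475 | 0.838 |
| 0.5 | 0.0625 | 0.0434 | 0.828 |

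With centre in the model, power is Φ(2.966 − 1.96) = 0.843 and type I error is 0.05.

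**Case B: allocation not separate by hospital.** Adding centre multiplies the standard error by √(1 − R²), where R² is the share of residual variance due to centre. From a power of 0.840 without centre (F-test), the results are:

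| R² (assumed) | Fall in standard error | Power with centre |
|---|---|---|
| 1% | 0.5% | 0.843 |
| 2% | 1.0% | 0.847 |
| 5% | 2.5% | 0.858 |
| 10% | 5.1% | 0.876 |

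For chance imbalance, the difference between arms in the share of patients from one centre has SD √(0.25 × 2/110) = 0.0674. An imbalance of 1.96 SDs is 0.132. It moves the unadjusted effect by 0.132 × D, which is 0.013, 0.026 or 0.053 SD for a centre difference of 0.1, 0.2 or 0.4 SD. The standard error is 0.135 SD.

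**What baseline adjustment already does.** Take a stable HbA1c difference of 0.4 SD between hospitals. Unadjusted, it is (0.4²/4)/(1 + 0.4²/4) = 0.04/1.04 = 3.8% of variance. With baseline in the model and an assumed correlation of 0.6, the remaining difference is 0.4 × (1 − 0.6) = 0.16 and the residual SD is √(1 − 0.36) = 0.8. So D = 0.16/0.8 = 0.2, and D²/4 = 1%. That is the lowest row of the Case A table.

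**The case against.** The strongest reply is that the listed terms include baseline values. A stable HbA1c difference between hospitals, and the imbalance it would cause, is therefore largely handled, and the single laboratory removes assay differences. This stands. A reader might infer from the missing term that all between-centre HbA1c variation stays in the error and that no centre imbalance is corrected. The documents do not support that for the baseline-adjusted model. It holds in full only for the unadjusted analysis of variance and for an outcome without a baseline value.

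A reader might also infer bias or false positives. Neither follows: under randomisation, leaving out a prognostic factor does not bias the estimate on average, and type I error stays at or below its nominal level.

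A third tempting inference is that allocation was stratified by centre, so that the usual rule of adjusting for stratification factors has been broken. The two sets of numbers suggest this but {16a} does not say it. Nor does the permission in {11d} for treatment to be adjusted show that the two hospitals treat differently.

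Two further replies have some force. An analysis plan that is not shown may add covariates. And the model is introduced for changes over time within arms, so it is unclear whether it is the main between-group analysis. Both argue for low severity. Neither removes the point, because {20a} does give a term list and neither of its routes to a between-group comparison contains centre.

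**Conclusion.** The point holds as a free improvement of low severity. Centre is missing from the listed terms and from the four-group analysis of variance, and site appears elsewhere only as an optional comparison.

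If allocation was separate by hospital, the cost is 0.2 to 1.5 points of power (0.841 to 0.828 against 0.843) and a type I error of 0.049 to 0.043. For HbA1c with baseline in the model, the low end of the range is the more plausible: a stable 0.4 SD centre difference comes out there under the assumed correlation of 0.6. If allocation was not separate, the gain from adding centre is of the same order, 0.3 to 1.8 points for an R² of 1% to 5%.

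All of these figures rest on an assumed centre effect and on equal-sized centres. Equal size gives the largest effect, so unequal centres would make it smaller.

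**What to change.** In {20a}, add centre (two levels) as a fixed effect to the model used for between-group comparison of HbA1c and of the continuous secondary outcomes measured in all four groups. Enter it alongside the baseline value where one exists; for monitoring frequency, centre enters without one. Keep the site comparison in {20b} as exploratory.

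The cost is one degree of freedom and one line of text. Centre is known for every participant, so no new data are needed. The change is sound whatever the two sets of random numbers turn out to be.

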## Interventions

### Intervention description {11a}

The Control group will undergo routine diabetes management: they will receive a standard portable glucose meter (Dnurse He pro wisdom; Beijing Dnurse Technology Ltd, Beijing, China) and blood glucose monitoring record book. The recommended timing and frequency of blood glucose monitoring will be explained to them according to national guidelines [9].

The Reminder group will receive the same materials as the Control group as well as a weekly telephone reminder to self-monitor blood glucose regularly. These reminders will be given by specially selected nursing undergraduates who have been trained in the rationale, interventions, and objectives of the study. Only nursing students who performed well on post-training testing are allowed to participate in the study. During the telephone call, students will ask participants whether they are self-monitoring regularly and, if not, what are the reasons.

The App group will receive a smart blood glucose meter (Dnurse SPUG mobile blood glucose uric acid tester; Beijing Dnurse Technology Ltd), and they will be led by a specially trainer researcher to download the Dnurse App 4.0.16 (dnurse.com/v2/app), designed to work smoothly with the smart blood glucose meter. The researcher will show the study participants how to open a personal account on the application and how to generate personalized diet and exercise programs, glucose control targets, and a blood glucose monitoring plan; how to access the food bank, disease information, and real-time blood glucose analysis and recommendations within the application; and how to set reminders to take medication and engage in other behaviors.

The App + Reminder group will receive the same materials and training as the App group, together with weekly telephone reminders like the Reminder group.

If members of the Control group and the Reminder group experience acute complications of diabetes, such as excessively high or low blood glucose, trial investigators will advise them to seek medical treatment as per standard procedures. If members of the App group and the App + Reminder group trigger a “critical value” alarm on the application, the customer service staff of the application’s manufacturer will call them by telephone and provide advice or information as per standard procedures. Both devices pass through ISO13485 and EU CE certifications.

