## Data collection and management

### Plans for assessment and collection of outcomes {18a}

All participants will complete baseline assessments and complete follow-up at the 3rd and 6th month after the intervention.

At baseline, demographic data will be collected on age, sex, ethnicity, educational level, marital status, employment status, current residence, and method of paying for medical expenses. Data will be collected on the following clinical variables: chronic complications related to diabetes, such as hypertension, cardiovascular disease, cerebrovascular disease, peripheral vascular disease, kidney disease, peripheral neuropathy, eye disease and diabetic foot. Any chronic complications of diabetes that arise during the study will be recorded at the 6th month. Similarly, data on acute complications related to diabetes will be collected at baseline, such as hypoglycemia and lactic acidosis or ketoacidosis; and current diabetes treatments, including non-drug therapy, oral hypoglycemic drugs, and insulin therapy. Any acute complications of diabetes that arise during the study will be recorded at the 6th month.

At baseline and again at the 6th month, all participants will be asked to fill out three questionnaires. In addition, the App and the App + Reminder groups will fill out a fourth questionnaire at 6th month, which assesses their satisfaction with the smartphone application and glucose meter (Table 2). At baseline and again at the 3rd and 6th month, data will be collected on height, weight, blood pressure and HbA_1c_. At the 3rd and 6th month, all participants will be asked about their frequency of blood glucose monitoring.

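### Baseline diabetes-treatment class is recorded before allocation but named in no analysis: a modest, avoidable loss of precision, mainly for monitoring frequency

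*Protocol article*

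**What the plan says.** All references are to the protocol article.

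- **Model terms, {20a}.** "These models will include intervention variables, time as a categorical variable represented by dummy variables, the interaction between intervention and time, and baseline values". The baseline term is not defined; its most natural meaning is the baseline value of the outcome being modelled.
- **What that model is for, {20a}.** "Differences between different time points within each group will be assessed for significance using generalized estimation equation".
- **Between-group tests, {20a}.** "differences between the four groups will be assessed for significance using the chi-squared test in the case, analysis of variance in the case", with a rank-sum test for skewed data. No covariate is stated for any of them.
- **What is recorded at baseline, {18a} and Table 1.** The clinical variables include "current diabetes treatments, including non-drug therapy, oral hypoglycemic drugs, and insulin therapy". Everyone is covered: "All participants will complete baseline assessments and complete follow-up at the 3rd and 6th month after the intervention". Table 1 schedules treatment again at month 6.
- **Monitoring frequency, {18a}.** "At the 3rd and 6th month, all participants will be asked about their frequency of blood glucose monitoring". Table 1 agrees and shows no baseline entry. It is a secondary outcome ({12}) and serves the second aim ({7}).
- **Allocation, {16a} and {16c}.** Participants are allocated once the baseline assessment is complete. No stratification by treatment class is described.

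**The concern.** The trial can enrol people on no drug, on oral drugs and on insulin. It is plausible that these groups differ in how often they test and in how their HbA1c moves. If so, a variable known for everyone before allocation is controlled neither in the randomisation nor in the analysis. The variance it explains stays in the error term, and any chance difference in, say, the share on insulin stays in the estimate.

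Monitoring frequency is the exposed outcome. For HbA1c, the model's baseline term already absorbs part of the between-person spread. Monitoring frequency has no baseline measurement, so that term, read as the outcome's own baseline, has nothing to hold, and the comparison is wholly unadjusted.

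At stake is precision on a secondary outcome that answers a stated aim, plus a small gain on the primary outcome.

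**Working it through.** **1. The plan's own figure.** {14} gives effect size 0.2, two-sided 0.05, power 0.9 and an F-test, with N = 220, raised to 264 for 20% loss. Reading 0.2 as Cohen's f with four groups, and using the noncentral F with λ = N·f² and N − 4 error df:

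- 90% power needs N = 265 for a main effect (1 df) or 359 for the four-group test (3 df), so 220 is not reproduced.
- N = 220 gives 84.0% (1 df) or 69.2% (3 df).
- 264 = 220 × 1.2, and 264 × 0.8 = 211.2, so about 211 are observed after the planned loss.

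The sample-size mismatch is a separate matter; nothing below depends on it.

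**2. Gain from adding treatment class.** With two equal halves, f = d/2, so f = 0.2 is a main effect of d = 0.4 SD. If class explains a share R² of the variance left by the other terms, then λ = N·f²/(1 − R²), with 2 further df used. The documents give no R²; 0.02 to 0.30 is an assumed range. For N = 211, N·f² = 211 × 0.04 = 8.44.

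| Assumed R² | λ | Standard error × √(1 − R²) | Power, main effect (1 df) | Power, four-group test (3 df) |
|---|---|---|---|---|
| 0 | 8.44 | 1.00 | 82.4% | 67.1% |
| 0.02 | 8.61 | 0.99 | 83.2% | 68.1% |
| 0.05 | 8.88 | 0.97 | 84.3% | 69.6% |
| 0.10 | 9.38 | 0.95 | 86.2% | 72.2% |
| 0.20 | 10.55 | 0.89 | 89.8% | 77.7% |
| 0.30 | 12.06 | 0.84 | 93.3% | 83.4% |

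With all 264 observed, main-effect power goes from 89.9% to 92.7%, 95.2% or 97.2% at R² = 0.1, 0.2 or 0.3.

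The rows at 0.02 and 0.05 are the assumed range for HbA1c once its own baseline is in the model: 0.8 to 1.9 points. The rows from 0.10 to 0.30 are the assumed range for monitoring frequency, which has no baseline value.

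**3. Chance imbalance.** Assume 30% on insulin and compare App with no App, 132 against 132. The standard error of the difference in insulin share is √(2 × 0.3 × 0.7/132) = 0.056, so the 95% limit is 1.96 × 0.056 = 0.11, or ±11 points. With 110 against 110 and an assumed prevalence of 20% to 50%, the limit is ±10.6 to ±13.2 points.

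If insulin users test 1 SD more often (an assumption), the estimate shifts by about 0.06 SD at one standard error and 0.11 SD at the 95% limit.

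**4. Steps 2 and 3 are the same cost.** Under the assumptions of step 3, class explains R² = 0.3 × 0.7 × 1² = 0.21. The unadjusted difference in means has variance 4/264 = 0.01515 (SD units squared). The part due to imbalance is 0.42/132 = 0.00318, and 0.00318/0.01515 = 0.21. The imbalance is already inside the unadjusted standard error, so it must not be added to the power loss.

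**The case against.** **It is a covariate preference in a condensed article.** This mostly stands. Leaving out a prognostic covariate does not bias a randomised comparison of means or inflate its type I error. The baseline term is loose enough that other variables are not ruled out, and an analysis plan not shown could name them. What remains is that {20a} does list its model terms, class is not among them, and the stated baseline term cannot serve monitoring frequency.

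**The premise is not in the documents.** This stands against a stronger reading. A reader might infer that insulin use is the main determinant of testing frequency. The nearest text, in {11a}, says only: "The recommended timing and frequency of blood glucose monitoring will be explained to them according to national guidelines". It mentions neither insulin nor treatment class. Class is a plausible predictor and no more, and even the assumed R² of 0.1 to 0.3 leaves 70% to 90% of the variance to other things.

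**The quoted model is not the between-group comparison.** Correct. {20a} assigns the GEE to changes within each group, so adding a term there would leave the ANOVA and rank-sum tests as they are. The remedy has to move the contrast as well.

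**The sizes flatter the case.** Partly right. The larger gains concern one secondary outcome, and {14} does not tie its effect size to that outcome. The ±11 points is a 95% limit rather than a typical imbalance. A reader might count it as a harm on top of the lost power; step 4 of the working shows that it is not.

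**The three treatments may overlap.** Correct. {18a} does not say that they are mutually exclusive, so someone on oral drugs and insulin has no defined level until the plan sets one.

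**Conclusion.** The point holds as an efficiency improvement. Baseline treatment class is available for everyone before allocation, is not used in the described randomisation, and is named neither in the GEE nor in the between-group tests. The documents do not support calling this a bias, a type I error problem or a contradiction.

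For HbA1c the gain is about 1 to 2 power points. For monitoring frequency it is about 4, 7 or 11 points at R² of 0.1, 0.2 or 0.3. These figures rest on an assumed R², on reading 0.2 as Cohen's f (0.4 SD for a main effect), and on 211 observed. If class explains little of the variance in testing frequency, the gain there is negligible too.

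**What to change.** In {20a} or the analysis plan:

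1. Take the between-group contrasts from the model, not from unadjusted ANOVA or rank-sum tests. For HbA1c this also brings its baseline value into the contrast.
2. State what the baseline term contains for each outcome, and that monitoring frequency has none.
3. Add baseline treatment class as a fixed covariate, above all for monitoring frequency, with mutually exclusive levels: any insulin; oral drugs without insulin; non-drug only.
4. Use only the class recorded before allocation. {11d} allows treatment to change during the trial and Table 1 records it again at month 6; a later class could itself be affected by the intervention. Fixing this in advance matters more because the analysts are not blinded ({17a}).

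The cost is a few lines of text and 2 degrees of freedom. No new data are needed.

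### Where month 0 is a GEE response, as it must be for the three questionnaires, the baseline covariate drops out of the intervention-by-time effect and adds no precision

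*Protocol article*

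**What the plan says.** All in the protocol article.

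- **Purpose of the GEE**, section {20a}: "Differences between different time points within each group will be assessed for significance using generalized estimation equation".
- **Its terms**, same section: intervention variables, "time as a categorical variable represented by dummy variables", then "the interaction between intervention and time, and baseline values". The section does not say which visits make up the response.
- **Group comparisons**, same section: "differences between the four groups will be assessed for significance using the chi-squared test", analysis of variance or a rank-sum test. No baseline adjustment is mentioned for any of these.
- **Visits**, section {18a}: for the questionnaires, "At baseline and again at the 6th month, all participants will be asked to fill out three questionnaires". For the physical measures and HbA1c, "At baseline and again at the 3rd and 6th month, data will be collected on height, weight, blood pressure" and HbA1c. For monitoring frequency, "At the 3rd and 6th month, all participants will be asked about their frequency of blood glucose monitoring".
- **Missing data**, section {20c}: the last available value is carried forward, with the baseline value used when no later one exists.
- **Questionnaire outcomes**, section {12}: each of the three scales is defined as a change from baseline.

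**The concern.** A baseline value can serve a longitudinal model in two ways. It can be a covariate that explains later values, or it can be the first response, against which change is measured. Listing it as a covariate in a model meant to compare time points raises the question of whether it is used both ways at once. If it is, the model looks baseline-adjusted while its intervention-by-time effect is not. A reader of the results would credit an adjustment that has had no effect, and the trial would give up precision that its own data could supply. The remaining group tests do not make up for this, because none is described as adjusted for baseline.

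**Working it through.** The plan gives no figure on this point and no correlation between visits, so there is nothing to reproduce. The check has three steps.

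**1. Which outcomes use baseline twice** (visits from section {18a})

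| Outcome | Visits (months) | Time dummies if all visits are responses | Time dummies if post-baseline only | Double use |
|---|---|---|---|---|
| DKN, HBQ, 2-DSCS | 0, 6 | 1 | 0 (no time term possible) | Forced, if the GEE is applied |
| HbA1c, BMI, blood pressure | 0, 3, 6 | 2 | 1 | Only if month 0 is a response |
| Monitoring frequency | 3, 6 | 1 | 1 | None (no baseline value) |

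For the middle row, the within-group purpose and the plural in "time as a categorical variable represented by dummy variables" point towards three time levels. One sentence covers every outcome, however, so the plural is weak evidence.

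**2. What the covariate does when month 0 is a response**

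Write the model as Y(i,t) = m(g,t) + c·B(i) + error. Here m(g,t) is a free mean for each group and visit, and B(i) is the participant's baseline, the same on all of that participant's rows. With complete data and one working covariance for everyone, the estimating equations make the mean residual zero in every group-by-visit cell. Hence

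- fitted m(g,t) = observed mean(g,t) − c·(mean baseline in g).

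The last term does not depend on t. In the difference between month 6 and month 0 within a group it cancels, leaving the raw mean change. The intervention-by-time effect is therefore the raw difference in mean change between groups, for any c. Carrying values forward under section {20c} supplies the complete data.

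Numerical check: one simulated trial per rho, 66 per group (264/4), visits 0, 3 and 6, SD 1.5 (assumed). The effect is one App arm against Control at month 6.

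| Assumed rho | GEE with covariate | GEE without | Raw change difference | Robust SE, with / without | ANCOVA estimate (SE) | GEE on months 3 and 6 |
|---|---|---|---|---|---|---|
| 0.3 | −0.342 | −0.342 | −0.342 | 0.282 / 0.282 | −0.386 (0.246) | −0.385 |
| 0.5 | −0.818 | −0.818 | −0.818 | 0.267 / 0.267 | −0.634 (0.243) | −0.652 |
| 0.7 | −0.284 | −0.284 | −0.284 | 0.198 / 0.198 | −0.371 (0.190) | −0.362 |

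The first three estimates agree under independence and exchangeable working correlation, and generalised least squares with an arbitrary covariance gives the same value. The model on months 3 and 6 tracks ANCOVA. These are single draws, so their SE ratios need not match the formula below.

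**3. Size of the precision loss**

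Assume equal variance s² at both visits and correlation rho. Per participant:

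- change score: 2s²(1 − rho)
- ANCOVA: s²(1 − rho²)
- ratio: 2(1 − rho)/(1 − rho²) = 2/(1 + rho)

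| Assumed rho | 2/(1 + rho) | Equivalent share of sample lost, 1 − (1 + rho)/2 |
|---|---|---|
| 0.3 | 2/1.3 = 1.54 | 35% |
| 0.5 | 2/1.5 = 1.33 | 25% |
| 0.7 | 2/1.7 = 1.18 | 15% |

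For comparison, an unadjusted ANOVA on month-6 values has variance s², so its ratio to ANCOVA is 1/(1 − rho²): 1/0.91 = 1.10, 1/0.75 = 1.33 and 1/0.51 = 1.96. Baseline adjustment gains on that test too.

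**The case against.** The algebra is not in doubt. The case on the other side concerns what the article commits to.

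- **The response visits are not written down.** For HbA1c, BMI and blood pressure, the listed terms also describe a sound model with months 3 and 6 as responses and baseline as covariate. A reader might infer that the primary HbA1c analysis is shown to be affected. The document does not support that: the within-group purpose favours month 0 as a response but does not settle it, and an article may leave this to the full plan. This part of the objection stands.
- **The GEE is not named as the test of treatment effect.** Section {20a} gives the four-group comparison to other tests and the within-group comparison to the GEE. This also stands. It does not rescue the covariate, which cancels from the within-group change as well, and the group tests state no adjustment either.
- **The questionnaire outcomes are defined as changes from baseline**, so the interaction estimates what was declared. That is correct, and under randomisation it is unbiased. A reader might infer bias from the double use; there is none on average. What is lost is precision and protection against chance baseline imbalance.
- **The loss depends on an unknown correlation** and shrinks as rho rises. This is true, so the size is given as a range. A reader might want a power loss for the trial; the article gives no correlation from which to compute one.

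**Conclusion.** The point holds in a limited form. If the GEE as listed is applied to DKN, HBQ and 2-DSCS, baseline is necessarily both response and covariate. For HbA1c, BMI and blood pressure this is conditional on month 0 being a response row. Monitoring frequency is outside the point. Where the double use occurs and the data are complete, the baseline covariate contributes nothing to the intervention-by-time effect, which has 1.54, 1.33 or 1.18 times the variance of ANCOVA at rho 0.3, 0.5 or 0.7. Those ratios rest on equal variances at the two visits and on assumed correlations.

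The conclusion concerns the interaction and the within-group changes. A group contrast read at month 6 from the same model would still carry some adjustment, but with a slope distorted because the baseline rows are regressed on themselves (0.53, 0.67 and 0.84 in the simulated trials at rho 0.3, 0.5 and 0.7). This is an efficiency improvement available at no cost, not an error that invalidates the analysis.

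**What to change.** State in the analysis text which visits are responses for each outcome, and separate the two purposes:

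- **Between-group effects on HbA1c, BMI and blood pressure:** GEE with months 3 and 6 only as responses, terms for intervention, time and their interaction, and the baseline value as covariate. Read the effect at month 6.
- **Between-group effects on DKN, HBQ and 2-DSCS:** ANCOVA of the month-6 score on intervention and the baseline score. The intervention coefficient is identical if change is used as the outcome, so the declared change outcomes are respected.
- **Within-group change from baseline, if also wanted:** keep baseline as a response and drop it as a covariate.

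The cost is a change of statistical wording. The data, visits and software stay the same. Because section {17a} leaves the analysts unblinded, the wording should be fixed before outcome data are analysed.
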